## Abstract

**Abstract:**

**Background:**

The implementation of genomic testing in pregnancy means that couples have access to more information about their child’s genetic make-up before birth than ever before. One of the resulting challenges is the management of genetic variations with unclear clinical significance. This population-based study will help to close this critical knowledge gap through a multidisciplinary cohort study of children with and without genomic copy number variants (CNVs) diagnosed before birth. By comparing children with prenatally-ascertained CNVs to children without a CNV, we aim to (1) examine their developmental, social-emotional and health status; (2) measure the impact of prenatal diagnosis of a CNV on maternal perceptions of child health, behavior and development; and (3) determine the proportion of prenatally-ascertained CNVs of unknown or uncertain significance that are reclassified as benign or pathogenic after 2 or more years.

**Methods:**

This study will establish and follow up a cohort of mother-child pairs who have had a prenatal diagnosis with a chromosomal microarray from 2013-2019 in the Australian state of Victoria. Children aged 12 months to 7 years will be assessed using validated, age-appropriate measures. The primary outcome measures will be the Wechsler Preschool and Primary Scale of Intelligence IV (WPSSI-IV) IQ score (2.5 to 7 year old’s), the Ages and Stages Questionnaire (12-30 months old), and the Brief Infant- Toddler Social and Emotional Assessment (BITSEA) score. Clinical assessment by a pediatrician will also be performed. Secondary outcomes will be scores obtained from the: Vineland Adaptive Behavior Scale, Maternal Postnatal Attachment Questionnaire, the Vulnerable Child Scale, Profile of Mood States, Parent Sense of Competence Scale. A descriptive analysis of the reclassification rates of CNVs after ≥2 years will be performed.

**Discussion:**

This study protocol describes the first Australian cohort study following children after prenatal diagnostic testing with chromosomal microarray. It will provide long-term outcomes of fetal genomic variants to guide evidence-based pre-and postnatal care. This, in turn, will inform future efforts to mitigate the negative consequences of conveying genomic uncertainty during pregnancy.

**Trial registration:**

ACTRN12620000446965p; Registered on April 6, 2020.

**Supplementary Information:**

The online version contains supplementary material available at 10.1186/s12887-021-02809-7.

## Background

Congenital anomalies, of which one third are chromosomal in origin, are the leading cause of perinatal death in Australia [1]. Prenatal screening for fetal chromosomal conditions is thus an important component of care for the 300,000 women who give birth in Australia each year. National guidelines recommend that voluntary screening, and the option of follow-up prenatal diagnosis, be provided to all pregnant women [2]. In 2019, Victoria recorded 409 prenatal diagnoses of major chromosome conditions, in a state population with 76,000 births per year (1 in 186 births) [3].

Over the past decade, technological advances have revolutionized genetic testing at every stage of reproduction [4]. Classical cytogenetics has been superseded by chromosomal microarray (CMA) as the gold standard for chromosomal assessment [5]. CMA interrogates the genome at a higher resolution than conventional karyotyping, allowing previously undetected submicroscopic copy number variants (CNVs) to be detected. A National Institute of Child Health and Human Development (NICHD) multicenter trial in the United States (US) provided the first large-scale report on the use of CMA for fetal chromosome analysis [6]. This landmark trial compared the accuracy of prenatal CMA to that of standard karyotyping and found that 5.8% of pregnancies with a fetal structural anomaly and a normal karyotype had a clinically significant CNV detected. Professional societies now recommend the use of prenatal CMA, particularly for the investigation of fetal structural anomalies [2, 7]. This has rapidly transitioned to being the ‘default’ investigation for any prenatal diagnostic test and accordingly in Victoria, the annual proportion of prenatal diagnoses utilizing CMA has exceeded 80% since 2015 [3].

The genomic imbalances detected by CMA include pathogenic CNVs (pCNVs) that are associated with well-described syndromes such as the 22q11.2 deletion syndrome and Prader-Willi / Angelman syndromes. However, with the ability of CMA to detect smaller genomic imbalances than conventional karyotype, comes a correspondingly higher detection rate of uncertain findings [8]. These variants of uncertain (or unknown) significance (VUS) are CNVs that have a variable amount of evidence available to assess their pathogenicity. Parental testing is often required to assist in interpretation of fetal VUS.

Fetal VUS present special clinical and ethical challenges compared with the pediatric setting [9]. VUS are reported in 5% of prenatal samples in Victoria, resulting in almost 100 women each year being informed that their unborn baby has an uncertain diagnosis [10]. These VUS include CNVs that may predispose to developmental disability or neuropsychiatric illness, but which are highly variable and unpredictable in effect (“neurosusceptibility CNVs”) [11]. Interpretation of uncertain variants during pregnancy requires more caution because where there is no apparent fetal phenotype, this information may bring more harms than benefits. There is currently no guidance for structured assessment and follow-up for these children after birth. Furthermore, our understanding of the clinical significance of variants is continuously evolving, and classification of CNVs may change over time without patients being notified of updated information.

Long-term outcomes of prenatally-ascertained CNVs are needed. To our knowledge, worldwide, there are only two cohort studies in progress investigating the postnatal outcomes of prenatal CNVs detected on CMA – the NICHD sponsored cohort from the United States [6] and the Belgium MicroArray Prenatal (BEMAPRE) consortium [12]. Generating new knowledge on long-term outcomes of fetal genomic variants will have a positive health impact by supporting (i) evidence-based pre- and postnatal care, and (ii) mitigating the negative consequences of conveying genomic uncertainty during pregnancy.

## Methods/Design

### Aims

The PALM cohort study will establish and follow-up a cohort of mother-child pairs who had a prenatal diagnosis of a CNV from 2013-2019 (inclusive) in the Australian state of Victoria. Victoria has approximately 78,000 births per year and a median maternal age of 31.5 years [13]. Approximately 2-3% of all pregnant women undergo prenatal diagnosis per year [14].

The study aims are to:
Compare the developmental, social-emotional and health status of children with a prenatal diagnosis of a prenatal CNV with those children with no CNV detected on CMA.Measure the impact of a prenatal diagnosis of a CNV on maternal perceptions of child health, behavior, and development.Determine the proportion of CNV ascertained prenatally that are reclassified from unknown or uncertain to benign or pathogenic after two or more years using contemporaneous curation resources.

### Study design

This cohort study that will recruit participants with an existing record of a prenatal CMA in the Victorian Prenatal Diagnosis Database (VPDD) between January 2013 and December 2019 inclusive. The VPDD is a unique population-based dataset housed at the Murdoch Children’s Research Institute (MCRI) that has been described in detail in prior publications [15]. The women who underwent prenatal diagnosis during the study period, and who had a live child at the time of discharge from hospital after birth, will be approached by mail from their clinical referrer to offer participation in the study. In brief, study participation will involve providing permission for data collection from the health records, completion of questionnaires, and an assessment of their child’s health and development.

### Study population

Each year the VPDD receives prenatal diagnostic testing results on approximately 150 pregnancies with CNVs, and 1000 pregnancies with no CNVs. We will recruit an equal number of participants with and without CNVs, frequency matched for fetal sex, trimester at prenatal diagnosis, maternal age group (by decade) and calendar year of testing. Due to the modifier of structural anomaly on childhood outcomes, women with fetal structural abnormalities will be excluded from the control group of pregnancies with no CNVs.

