### Pre-screening

The aim of the pre-screening stage is to accurately identify potential eligible participants, and to avoid contacting women who may have experienced a perinatal loss in the relevant pregnancy. For this reason, the involvement of the clinical referrer in the recruitment process is considered essential.

Pre-screening will include the following:

(i) Pre-screening stage 1. Audit of prenatal CMA results at the VPDD to identify potential participants based on prenatal diagnosis results. This will be performed by the study team at the MCRI who manage the VPDD. A list containing all records with a CNV detected on CMA during the study period will be generated and categorized into pCNV or VUS groups. A list of non-CNV records, where there is no fetal structural abnormality, will also be created as the control cohort. Each record will have the limited individual identifiers from the contributing cytogenetic laboratories, available under the existing VPDD ethics protocol (i.e., first three letters of maternal surname and first name, date of testing, type of test, date of birth).

(ii) Pre-screening stage 2. This list of potential participants from the VPDD with the limited identifiers will be sent in a secure file to the respective laboratories that performed the CMA testing using Research Electronic Data Capture (REDCap), a secure web application specifically designed to support online and offline data capture for research studies [17, 18].

(iii) Pre-screening Stage 3. Individual lists of potential participants for each clinical practice location will be generated by the participating laboratories. The vast majority will be captured through the five public hospital fetal medicine units: The Royal Women’s Hospital, The Mercy Hospital for Women, Monash Medical Centre, Sunshine Hospital and Box Hill Hospital. Approximately 20% will be from private obstetricians and regional referrals.

(iv) Pre-screening Stage 4. Examination of health records for exclusion criteria by the clinical referrers. The protocol will vary depending on whether the referral came from a public hospital or private practice.

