### Statistical methods of analysis and power calculations

#### Objective 1:

The primary outcome for the 2–7-year-old group is the WPPSI-IV full IQ score. The WPPSI-IV is standardized to be normally distributed with a mean of 100 and standard deviation of 15 in the general population (variance of 30). It is therefore possible to perform the primary analysis as a single group comparison by t-test of the WPPSI-IV full IQ score in the children enrolled in this study with the population norm. A between-group analysis of the WPPSI-IV for the CNV study group and control (non-CNV) group cohorts will be done. The results from the children with VUS will be analyzed separately from those with pathogenic CNVs (pCNVs).

If 300 participants with VUS are enrolled, this will yield > 95% power and 95% confidence to detect a 3-point difference (0.2SD) in mean IQ from the norm assuming that the standard deviation is 15.

Our study cohort of women with VUS are a heterogenous group with varying indications for testing. As the presence of a fetal structural abnormality is likely to be a modifier of all assessed outcomes, a stratified analysis of the CNV cohort with and without this indication for prenatal diagnosis will be performed. An audit of the VPDD data shows that those with a fetal structural abnormality comprise two thirds of the VUS study cohort, leaving 100 to study without such an abnormality. The required sample size is therefore a minimum of 87 women without a fetal structural abnormality in each of the study and control cohorts to detect a 3-point difference in mean IQ (95% power, 95% confidence).

For the group with pCNVs, a larger difference in mean IQ is expected between those with pCNVs and those without any CNV. A minimum of 13 participants in the pCNVs cohort is required to detect a mean difference of 8 IQ points with 95% power and 95% confidence. It is expected that this analysis can be performed on the subgroup with the most common pCNV (22q11.2 deletion syndrome), which is detected prenatally in approximately 7 cases per year. If 100% progressed to live outcome, there would be at least 35 children in the cohort (born from 2013-2018) that would be able to perform the WPPSI-IV. Less than 50% would be required to be available for recruitment to meet the minimum sample size of 13.

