#### For the 12–24-month-old group, the ASQ-3 and ASQ:SE-2 scores are the primary outcomes

Scores for individual items are summed to give an overall continuous score for each of the domains in the ASQ-3 and ASQ:SE-2. In addition to using scores as continuous outcomes, we will categorize the scores according to the recommended scores for typical development, need for monitoring, and need for further assessment. We will collapse these three categories into a binary variable (those with typical development vs those with a need for monitoring or further assessment [i.e., potential atypical or delayed development]). The differences in those with typical and ‘atypical’ scores will be compared among the CNV subgroup using chi-squared test for proportions or Fisher’s exact test as appropriate.

#### Objective 2

The primary outcome will be the BITSEA score. We will analyze the data according to the subgroup of CNV result (pCNV, VUS) compared with controls, stratified by age. The secondary outcomes will be the Maternal Postnatal Attachment Questionnaire (MPAS), Vulnerable Child Scale (VCS), Profile of Mood States (POMS), and the Parent Sense of Competence Scale (PSOC). For the secondary outcomes, we will compare group differences in responses using mixed effect regression models. We will report mean values for the parent report of child behavior, parenting competence, attachment, perceived child vulnerability and parent mood. Parent gender, country of birth, education, employment status, and child sex will be adjusted as covariates.

#### Objective 3

We will compare the classifications given at the time of issue of the prenatal report and the current classifications in 2020-21 according to the issuing laboratory’s protocols. The proportion of pCNVs, VUS and benign variants will be compared between the prenatal and 2-year postnatal classifications using chi-squared test for proportions.

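### Objective 2's VUS-versus-control contrasts mix the effect of the VUS result with that of a fetal structural abnormality, which two thirds of the VUS cohort and no controls have

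*Protocol article*

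**What the plan says.** **Controls.** The Study population section says "women with fetal structural abnormalities will be excluded from the control group of pregnancies with no CNVs", and gives as its reason that anomaly modifies childhood outcomes. Pre-screening stage 1 builds the list accordingly: "A list of non-CNV records, where there is no fetal structural abnormality, will also be created as the control cohort". Controls are "frequency matched for fetal sex, trimester at prenatal diagnosis, maternal age group (by decade) and calendar year of testing"; structural abnormality is not a matching factor.

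**CNV cohort.** No such exclusion applies. Objective 1 reports from an audit of the database that "those with a fetal structural abnormality comprise two thirds of the VUS study cohort, leaving 100 to study without such an abnormality". It also says that "the presence of a fetal structural abnormality is likely to be a modifier of all assessed outcomes", and for that reason plans a stratified analysis of the CNV cohort by this indication. It then sizes a comparison of abnormality-free pregnancies in both cohorts.

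**Objective 2.** The primary outcome is the BITSEA: "We will analyze the data according to the subgroup of CNV result (pCNV, VUS) compared with controls, stratified by age". The secondary outcomes (MPAS, VCS, POMS, PSOC) use mixed effect regression. On adjustment: "Parent gender, country of birth, education, employment status, and child sex will be adjusted as covariates". Structural abnormality appears neither among the strata nor among the covariates.

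**The concern.** The protocol names a factor that it expects to affect every outcome, and then sets its frequency at about two thirds in one group and zero in the other. In a whole-group VUS-control contrast, the effect of the variant and that of the malformation arrive together. Regression cannot pull them apart except by modelling assumption, because no child has an abnormality without a CNV.

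This matters most for Objective 2. Its aim is the effect on the mother of being told of a CNV, and the Discussion (Women's experience of prenatal VUS) expects the study to show whether disclosing a VUS does harm. A mother whose fetus had a structural abnormality may see her child as more vulnerable whatever the microarray showed. Comparing her with a mother who had neither finding does not isolate disclosure. The bias probably points towards harm from the VUS, and the Translation plan contemplates structured follow-up of these children.

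**Working it through.** **Inputs from the article.** Abnormality share: 2/3 in VUS (Objective 1), 0 in controls (Study population; Pre-screening). Planned numbers: 267 VUS and 358 controls (Sample size). IQ SD 15 and target difference 3 points (Objective 1).

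**Assumption.** The malformation effect D is not given anywhere in the article, so a range is shown.

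**The plan's own figure for the abnormality-free comparison.** Objective 1 asks for at least 87 per cohort for 3 points at 95% power, two-sided 5%.
- n per group = 2 × variance × (1.960 + 1.645)² / 3².
- With the printed variance of 30: 2 × 30 × 12.99 / 9 = 86.6, so 87. The figure reproduces.
- With SD 15 (variance 225): 2 × 225 × 12.99 / 9 = 649.7, so 650. At 87 v 87 the power is about 26%.

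The variance error is a separate matter. It counts here only because it makes the clean comparison look better powered than it is.

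**Bias in the whole-group VUS contrast if the VUS has no effect.** Bias = (2/3 − 0) × D.

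**Chance of a significant result for IQ.** SE = 15 × √(1/n₁ + 1/n₂), two-sided 5%, normal approximation. The WPPSI-IV is given to the older cohort only. Objective 1's own 22q11.2 example counts 35 children from 7 cases a year, that is 5 of the 7 years. 358 × 5/7 ≈ 256 controls; 89 × 5/7 ≈ 64 abnormality-free VUS; 3 × 64 = 192 VUS in all.

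| Assumed D (IQ points) | Bias | 192 v 256 (SE 1.43) | 267 v 358 (SE 1.21) |
|---|---|---|---|
| 3 | 2.0 | 29% | 38% |
| 5 | 3.3 | 64% | 78% |
| 8 | 5.3 | 96% | 99% |

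An assumed D of 4.5 points gives 2/3 × 4.5 = 3.0, the whole target difference.

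**Objective 2 scales.** These questionnaires go to all children aged 12 months or older (Table 2), so 267 v 358 is the relevant ceiling. In SD units the three rows are malformation effects of 3/15 = 0.20, 5/15 = 0.33 and 8/15 = 0.53 SD, and the last column applies if every questionnaire is returned and the age strata are combined. Within a single age stratum the chance is lower; the expected bias is the same if the two-thirds share holds there.

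**Precision of the restricted comparison.** Abnormality-free VUS: 267 / 3 = 89. Detectable difference at 80% power = (1.960 + 0.842) × SE.
- 89 v 358: 2.80 × 1.78 = 5.0 points.
- 64 v 256: 2.80 × 2.10 = 5.9 points.

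**The case against.** **The protocol already deals with this.** For Objective 1 that is largely right. The stratified analysis covers the CNV cohort, and an abnormality-free comparison with controls is explicitly sized. A reader might infer that every CNV-control contrast in the study is confounded with no clean alternative; the article does not support that. What remains for Objective 1 is which VUS contrast carries the inference.

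**The reason for stratifying refers to all assessed outcomes, so Objective 2 may be covered.** This is a possible reading, and a condensed article may leave detail to the full protocol. But the sentence sits under Objective 1, and Objective 2 states its own strata and covariates without the factor. Someone following that text would run the whole-group contrast.

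**The primary WPPSI-IV analysis is not a control contrast.** Correct: it is a one-group test against the population norm. The IQ probabilities above concern the additional between-group analysis. The malformation effect would also enter the VUS mean in the test against the norm, but the figures here do not describe that test.

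**The 38%, 78% and 99% figures overstate the IQ risk.** They do, unless every child has a WPPSI-IV; 29%, 64% and 96% fit the older cohort better.

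**The same restriction should not be imposed on pathogenic CNVs.** This stands. The two-thirds share is stated for VUS only, and the Background ties pathogenic CNVs to recognised syndromes. An anomaly may be part of what the CNV does, and restricting to unaffected children would then remove part of its effect.

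**Parent gender in the covariate list.** It is constant, because only the biological mother is eligible. It drops out of the model and biases nothing.

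**Conclusion.** The concern holds for VUS in Objective 2, where the stated analysis gives no contrast free of the malformation. It holds for Objective 1 only in that the unrestricted VUS-control contrast is not marked as unable to isolate the variant. The bias equals two thirds of the malformation effect. That multiplier rests on the protocol's own audit share holding among the women recruited. The size of the malformation effect is an assumption throughout, and so are the 5/7 fraction for WPPSI-IV testing and complete questionnaire return. The documents do not show that the bias will reach any particular size, nor that pathogenic CNVs have the same imbalance.

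**What to change.** 1. State under Objective 2 that the stratification by structural abnormality described in Objective 1 applies to the BITSEA, MPAS, VCS, POMS and PSOC.
2. For VUS, in Objectives 1 and 2, base any inference about the variant or its disclosure on the comparison restricted to pregnancies without a structural abnormality.
3. Report the whole-group and with-abnormality VUS contrasts as descriptive, and say that they do not isolate the CNV because no control has an abnormality.
4. For pathogenic CNVs, report both the unrestricted and the abnormality-free contrast, and explain that they answer different questions.

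**Cost.** No new data are needed, since the control list and the audit both show that the database identifies structural abnormality. The cost is precision. The main VUS contrast falls to about 89 v 358, detecting about 5 IQ points at 80% power (about 6 with 64 v 256 in the WPPSI-IV subset) against a 3-point target, and two thirds of the VUS children move to a descriptive role in the control comparison. The article should state this, with the detectable difference computed from SD 15.

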### Inclusion criteria

The biological mother (gestational carrier) is the most relevant parent/legal guardian to consent for participation as she was the individual that underwent the prenatal diagnostic procedure. She will be eligible by meeting the following criteria:
Prenatal CMA result reported in a singleton pregnancy during January 2013 - December 2019 inclusiveAt least 18 years of age at enrolmentAble to provide informed consent in EnglishLive infant outcome from index pregnancyPrimary care-giver for the child at the time of hospital discharge after birthCapable of providing consent on behalf of herself and her childAble to complete the parental questionnaires and accompany her child for study assessmentsResides in Victoria

